### Study therapy

Eligible subjects will be randomly assigned to wear standard SCL SEED 1dayPure UP or SEED 1dayPure UP Flex with + 0.50 D add power in the peripheral areas (SEED Co., Ltd., Tokyo, Japan) (Fig. 1). Contact lens power correction will be determined based on the results of the cycloplegic refraction. Slit-lamp microscopy examination of anterior ocular segment and interviews will be performed 2 weeks and 1, 3, 6, 9, 12, 15, 18, 21, and 24 months after the allocation of the subjects. Cycloplegic refraction, AL, and aberrations (Wavefront sensor, Topcon Corporation, Tokyo, Japan) will be measured 2 weeks and 0.5, 1, 1.5, and 2 years after the allocation. If myopia progresses and the decimal VA with SCL becomes less than 1.0, the contact lenses will be replaced. A flow chart of the study is shown in Fig. 2.

**Fig. 2 Fig2:**
[figure not shown]
Study flow chart. A same package is used for both multifocal and SCLs, so that subjects and study personnel could not identify the type of SCL

We planned to give the patients only a 3-month supply of contact lenses, and require them to visit the clinic every 3 months. Due to the prevalence of coronavirus, even if hospital follow-up visits do not occur as per the protocol, the contact lenses are being sent to minimize dropouts.

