### Secondary endpoints

The change of spherical equivalent at each observation time point 0.5, 1, 1.5, and 2 years compared to at baseline.Changes in AL at each observation time point 0.5, 1, and 1.5 years compared to at baseline.Changes in AL and spherical equivalent at each observation time point 0.5, 1, 1.5, and 2 years compared to at the time of enrollment.Observation of the changes in the eyes and extraocular areas by slip-lamp microscopy examination from the start of the study to the end of the observation period (or at the time of study discontinuation).Incidence of adverse events and medical device-related adverse events from the start of the study to the end of the observation period (or at the time of study discontinuation).

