### Outcome measurements

AL was measured using noncontact partial coherence interferometry. The cycloplegic refraction, objective spherical power, astigmatic power and axis, the objective spherical equivalent power, and the mean corneal refractive power will be measured using an auto-refractometer under Cyplegin 1% eye drops. Decimal VA will be examined by orthoptists using the Landolt-C chart. Total higher order, coma-like, spherical-like and spherical aberrations, as well as pupil diameters for cornea/ ocular were measured with or without cycloplegic agents by using the Wavefront sensor KR-1 W®. The difference of each measurement points from the baseline is evaluated.

Wearing conditions of SCL and cornea/conjunctiva will be examined by the slip-lamp microscopy at each follow-up visit. Subjects’ background characteristics will be obtained during the interview at the first visit to the study site. If a serious adverse event occurs, it should be reported to the School Superintendent in accordance with the procedures. Serious adverse events should be listed in the paper. Medical interviews and slit-lamp microscopy examinations will be conducted at each hospital visit to identify adverse events. Clinically important adverse events will be described in the paper. If any health damage occurs in relation to this clinical research, it will be compensated by the clinical research insurance purchased for this clinical research.

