### Data monitoring and audits

Contracted monitoring organization is INCREASE Co., Ltd. The data center will perform the central data monitoring using the electronic data of the case report forms. Central monitoring will identify missing values and ask each facility to make up for them. If it is truly deficient, it was noted. Data monitoring at study sites will also be performed by using sampled subjects. Results will be reported after monitoring. If any data is missing, the missing values are to be complemented by the single-assignment method.

Contracted auditing organization is INCREASE Co., Ltd. Results will be reported after audit.

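### Lenses keep being supplied when visits are missed, while the only active search for adverse events described takes place at visits, so adverse-event incidence may be under-counted

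*Protocol article*

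**What the plan says.** All references are to the protocol article.

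- **Supply (text with the Fig. 2 study flow chart).** Supply was first tied to attendance: "We planned to give the patients only a 3-month supply of contact lenses, and require them to visit the clinic every 3 months". The next sentence loosens that tie for the pandemic: "even if hospital follow-up visits do not occur as per the protocol, the contact lenses are being sent to minimize dropouts". The tense shows that this is current conduct.
- **Detection (Outcome measurements).** "Medical interviews and slit-lamp microscopy examinations will be conducted at each hospital visit to identify adverse events". No telephone call, diary or other contact is described for a visit that does not happen.
- **Schedule (Study therapy).** Slit-lamp examinations and "interviews will be performed 2 weeks and 1, 3, 6, 9, 12, 15, 18, 21, and 24 months after the allocation of the subjects", which makes ten occasions.
- **Endpoints (Secondary endpoints).** "Incidence of adverse events and medical device-related adverse events from the start of the study to the end of the observation period", or to discontinuation if that comes first. Slit-lamp changes are a separate endpoint over the same period. No denominator is stated for the incidence.
- **Serious events (Outcome measurements).** "If a serious adverse event occurs, it should be reported to the School Superintendent in accordance with the procedures". This rule is not tied to a visit.
- **Missing data (Data monitoring and audits).** Central monitoring looks for missing values, asks the sites to supply them, and notes those that cannot be supplied. Then: "If any data is missing, the missing values are to be complemented by the single-assignment method". No exception is made for safety data.

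**The concern.** Taken together, these rules let lens wear continue while the one active detection method described stops. The safety endpoints still cover that time.

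A later interview may bring out symptoms that the child or parent remembers. It cannot show a corneal or conjunctival sign that has already cleared, and it finds nothing in a child who does not come back. The single-assignment rule adds a difficulty: applied to a missed slit-lamp examination, it would supply a finding that nobody made.

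The Discussion says that the effect of soft contact lens wear in young children is not yet fully understood, so the absolute frequency of device-related events is a result that readers will use. If it is too low because some wear was not examined, the published table should let them see that.

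**Working it through.** The article gives no adverse-event rate, no missed-visit rate and no safety sample size, so there is no stated figure to reproduce. The check has two parts.

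**1. How long can wear go unexamined?**
The quarterly schedule gives 24 / 3 = 8 intervals. If *k* consecutive quarterly visits are missed, the gap between examinations is 3 × (*k* + 1) months:

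| Consecutive visits missed | Gap between examinations |
|---|---|
| 0 | 3 months |
| 1 | 6 months |
| 2 | 9 months |
| 3 | 12 months |

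Each missed quarterly visit corresponds to 1 / 8 = 12.5% of a child's planned follow-up. This treats a visit as covering the quarter before it. That is reasonable for an interview but generous for a slit-lamp examination, which sees one day.

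**2. How large could the under-count be?**
Let *m* be the share of wear time without examination or interview, and *r* the share of events in that time recovered later, at a subsequent interview or by spontaneous report. Assume a constant event rate and full detection in examined time. Then

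observed / true events = 1 − *m*(1 − *r*).

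Neither *m* nor *r* is in the document. As an assumption, take *m* from 10% to 40% (0.8 to 3.2 of the 8 quarterly intervals) and *r* from 0 to 1:

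| *m* | *r* = 0 | *r* = 0.5 | *r* = 0.8 | *r* = 1 |
|---|---|---|---|---|
| 10% | 0.90 | 0.95 | 0.98 | 1.00 |
| 20% | 0.80 | 0.90 | 0.96 | 1.00 |
| 30% | 0.70 | 0.85 | 0.94 | 1.00 |
| 40% | 0.60 | 0.80 | 0.92 | 1.00 |

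For example, *m* = 20% and *r* = 0.5 gives 1 − 0.20 × 0.50 = 0.90. Under this model the count is too low or correct, never too high. Recovery should be high for serious or memorable symptomatic events and low for asymptomatic signs that resolve, so the left-hand columns apply mainly to slit-lamp findings.

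**The case against.** A reader might infer that unexamined wear is counted as event-free, and that the safety endpoint is therefore understated. The documents do not support that.

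- **No scoring rule or denominator is given.** Nothing says that a missed visit counts as no event. Incidence may be meant as the proportion of children with an event rather than a rate over wear time.
- **Visits are the only route described, not the only route stated to exist.** Serious events have their own reporting rule, and later interviews can recover symptoms. The full protocol may hold a remote-contact procedure that a condensed article leaves out.
- **Missing examinations do not simply vanish.** Central monitoring is to query missing values and note those that are truly absent.
- **A sharper number is not available.** With 50 children per arm for 2 years (50 × 2 = 100 child-years) and no events, the 95% upper bound is −ln(0.05) / 100, or 3.0 per 100 child-years. On 75 or 50 child-years it is 4.0 or 6.0. The larger figures need assumed missed-visit shares of 25% and 50%, no later recovery and full follow-up, although Sample size and randomization expects about 20% of subjects to be unevaluable.
- **Some loss is not due to mailing.** A sign that appears and clears between two attended visits is missed in any case.
- **Bias between arms is not shown.** Subjects and examiners are masked, the packages are the same, and the mailing statement covers both arms.
- **There is no contradiction of wording.** The mailing is openly declared as a departure from the schedule.

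All of this limits the claim to a risk of unknown size. It does not remove the point. The article itself states both the detection rule and the departure from it, so the gap arises from two written rules acting together, not from silence alone. Noting a missing value does not replace an interview, and the single-assignment sentence leaves open what is then done with it.

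**Conclusion.** The point holds as a risk to ascertainment. Non-serious events and transient slit-lamp signs may be under-counted during wear that continues without a visit. On the assumptions shown, the under-count ranges from none, if all events are recovered later, to 40%, if 40% of wear is unexamined and nothing is recovered. The document cannot narrow that range.

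The main effect is on absolute incidence within each arm. A distorted comparison would need missed visits or recovery to differ by arm, and the document gives no sign of that. The argument does not touch the primary axial-length analysis. Severity is minor, limited to the secondary safety endpoints. Whether sending lenses without a visit is clinically acceptable is not judged here.

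**What to change.** From now on:

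1. When lenses are sent without a visit, hold the adverse-event interview due at that visit remotely, and record on the case report form that no slit-lamp examination took place.
2. Exclude missed slit-lamp and adverse-event data from the single-assignment rule under Data monitoring and audits.
3. Report incidence by arm in two ways: per child, and per observed child-time. Observed time means interview-covered time for symptoms and examination-covered time for slit-lamp findings.
4. Report mailed supplies and missed examinations by arm. Tabulate intervals already past from the visit records.
5. Reconcile Study therapy, the text with Fig. 2 and Outcome measurements, stating how adverse events are sought when a visit does not occur. If the full protocol already provides for this, one sentence is enough. No supply or other clinical rule is proposed.

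The cost is a short remote interview per mailed supply, in place of one already scheduled, plus one case report form field and two further tabulations. Past unexamined intervals cannot be recovered, and rates over observed time may look slightly less favourable.

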### Outcome measurements

AL was measured using noncontact partial coherence interferometry. The cycloplegic refraction, objective spherical power, astigmatic power and axis, the objective spherical equivalent power, and the mean corneal refractive power will be measured using an auto-refractometer under Cyplegin 1% eye drops. Decimal VA will be examined by orthoptists using the Landolt-C chart. Total higher order, coma-like, spherical-like and spherical aberrations, as well as pupil diameters for cornea/ ocular were measured with or without cycloplegic agents by using the Wavefront sensor KR-1 W®. The difference of each measurement points from the baseline is evaluated.

Wearing conditions of SCL and cornea/conjunctiva will be examined by the slip-lamp microscopy at each follow-up visit. Subjects’ background characteristics will be obtained during the interview at the first visit to the study site. If a serious adverse event occurs, it should be reported to the School Superintendent in accordance with the procedures. Serious adverse events should be listed in the paper. Medical interviews and slit-lamp microscopy examinations will be conducted at each hospital visit to identify adverse events. Clinically important adverse events will be described in the paper. If any health damage occurs in relation to this clinical research, it will be compensated by the clinical research insurance purchased for this clinical research.

### Statistical analyses

All data will be analyzed based on the “intention-to-treat” analysis. The primary analysis will be performed in the full analysis set (FAS), and robustness of the results will be explored through sensitivity analysis in the per-protocol set (PPS). The full analysis set (FAS) refers to all subjects who consented to start wearing contacts, and the PPS refers to subjects who were able to wear contacts on schedule for 2 years. No interim analysis is planned.

#### Data management

INCREASE Co., Ltd., Tokyo, Japan, will act as a data center, and manage and handle study data that include data cleaning.

#### Data analyses

Summary statistics will be calculated for test values and change values at the end of the observation period (24 months) from the baseline (2 weeks). Between-group comparisons will be performed using the mixed effects model for repeated measures in both eyes, and individuals as random effects. The significance level is set at 5% (two-sided). All statistical analyses were performed using SAS version 9.4 (SAS Institute Inc., Cary, NC, USA) software.

### Data monitoring and audits

Contracted monitoring organization is INCREASE Co., Ltd. The data center will perform the central data monitoring using the electronic data of the case report forms. Central monitoring will identify missing values and ask each facility to make up for them. If it is truly deficient, it was noted. Data monitoring at study sites will also be performed by using sampled subjects. Results will be reported after monitoring. If any data is missing, the missing values are to be complemented by the single-assignment method.

Contracted auditing organization is INCREASE Co., Ltd. Results will be reported after audit.

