### Primary endpoint

The change of axial length (AL) at the end of the observation period compared to the baseline.

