### Sample size and randomization

The planned sample size is 50 subjects each at both the Kyoto Prefectural University of Medicine and the University of Tsukuba, i.e., a total of 100 subjects. The sample size is based on the previous published data. Progression of myopia with multifocal SCL and that with standard therapy such as glasses were assumed to be − 0.54D/year and − 0.84D/year, respectively, based on a previous study conducted in USA [11], and standard deviation (SD) was assumed to be 0.66D based on our previous study [12]. Considering that approximately 20% of the subjects would be unevaluable due to study withdrawal, etc., 50 subjects in each group and a total of 100 subjects were determined to be included in this study to detect a between-group significance (alpha = 0.05, two-sided and power = 90%).

Adaptive randomization will be performed to avoid any accidental bias between the two groups. Adaptive stratified sampling will be carried out using the minimization method with genders, grades, and study sites as allocation factors. Randomization is done by an outside clinical research support company. Once consent is obtained, a fax of the case entry is sent and the allocation of the case is sent back.

The meaning of “double-masked” is that both the subjects and the examiners do not know who is in the target group and who is in the control group. An external data center knows whether each case is a subject or a control. The analysis is done in the data center, but in a different department than the allocation.

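### The protocol prescribes single imputation for any missing value; if 24-month axial lengths are filled this way, the primary comparison either reports too small a standard error or is biased, depending on the unnamed variant.

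*Protocol article*

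**What the plan says.** - **Missing data** (Data monitoring and audits): sites are first asked to supply missing values. Then: "If any data is missing, the missing values are to be complemented by the single-assignment method".
- **Endpoint** (Primary endpoint): "The change of axial length (AL) at the end of the observation period compared to the baseline". Under Study therapy, axial length is measured at 2 weeks (the baseline) and at 0.5, 1, 1.5 and 2 years.
- **Model** (Data analyses): "Between-group comparisons will be performed using the mixed effects model for repeated measures in both eyes, and individuals as random effects". Imputation is not mentioned there.
- **Analysis sets** (Statistical analyses): "The primary analysis will be performed in the full analysis set (FAS), and robustness of the results will be explored through sensitivity analysis". That second analysis is restricted to the per-protocol children. The FAS is defined by agreement to start wearing lenses, whereas "the PPS refers to subjects who were able to wear contacts on schedule for 2 years".
- **Expected loss** (Sample size and randomization): "approximately 20% of the subjects would be unevaluable due to study withdrawal, etc".
- **Pandemic provision** (text under Fig. 2): "even if hospital follow-up visits do not occur as per the protocol, the contact lenses are being sent to minimize dropouts".

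**The concern.** Single imputation gives each missing value one invented figure, which the model then treats as a measurement. Two kinds of harm can follow.

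- Filling with a group mean, a regression prediction or a single draw makes the sample look larger, or less variable, than it is, so the standard error is too small.
- Carrying the last value forward freezes an eye that is expected to keep growing, so that child's two-year change is recorded too low.

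The rule as written reaches the primary endpoint, and the FAS keeps children who later drop out. The significance test and confidence interval for 24-month axial length are therefore exposed. A later SAP could name the variant, but the choice of single imputation is already made here.

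**Working it through.** The plan gives no figure for the effect of imputation, so there is none to reproduce. Its one relevant number is the 20% allowance: of 50 children per group, 10 lost and 50 × 0.8 = 40 evaluable.

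**1. Group-mean imputation (closed form).** Let n be the group size, m = (1 − d)n the number observed, and s the SD of the observed changes.

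- The filled-in mean equals the observed mean, so its true variance is s²/m.
- The filled values add nothing to the sum of squares, so the reported variance is about (m·s²/n)/n = m·s²/n².
- Reported/true SE = √[(m/n²)·m] = m/n = 1 − d.
- Actual size of a nominal 5% test = 2[1 − Φ(1.96(1 − d))].

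| Missing d | SE ratio | 1.96(1 − d) | Type I error |
|---|---|---|---|
| 5% | 0.95 | 1.862 | 6.3% |
| 10% | 0.90 | 1.764 | 7.8% |
| 20% | 0.80 | 1.568 | 11.7% |
| 30% | 0.70 | 1.372 | 17.0% |

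The ratio does not depend on the scale of the outcome, so it applies to axial length, for which the protocol gives no SD.

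**2. Pooled-mean imputation.** With equal loss, the difference and its reported SE both shrink by the factor 1 − d. Type I error stays near 5%, but at 20% missing the estimated effect is 20% too small.

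**3. Other variants, by simulation.** There were 6,000 simulated trials with 50 children per arm, 10 lost per arm at random, and the last visit spread evenly over baseline, 0.5, 1 and 1.5 years. Because no axial-length inputs are given, the refraction figures stand in. Rates "were assumed to be − 0.54D/year and − 0.84D/year, respectively", so control change is 2 × −0.84 = −1.68 D over two years. The stated SD of 0.66 D is taken as the SD of two-year change, with 85% of its variance assumed to come from child-level slopes. One value per child was used. With no true effect:

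| Method | Reported/true SE | Type I error |
|---|---|---|
| Observed children only | 1.00 | 5.1% |
| Group mean | 0.80 | 11.5% |
| Regression on last visit | 0.87 | 8.9% |
| Single random draw | 0.88 | 8.1% |
| Last value carried forward | 1.19 | 2.3% |

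A separate simulation of random-donor imputation gave 10.8%.

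**4. Carry-forward bias.** With linear growth and the last visit spread as above, a dropout has shown on average (0 + 0.25 + 0.5 + 0.75)/4 = 0.375 of the two-year change, so 0.625 of it is lost.

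- Equal 20% loss: attenuation is 0.20 × 0.625 = 12.5%. A true 0.60 D difference becomes 0.60 × 0.875 = 0.525 D (simulated 0.524 D, or 13%).
- Loss of 10% v 30% with no true effect: the false difference is (0.30 − 0.10) × 0.625 = 12.5% of the two-year change, or 0.125 × 1.68 = 0.21 D (simulated 0.210 D, type I error 24%).
- Loss of 15% v 25%: the false difference is 0.10 × 0.625 = 6.25% of the two-year change.

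These are proportions because the protocol gives no axial growth rate. If one assumes 0.3 mm/year (0.6 mm over two years), the last two are about 0.075 and 0.04 mm, and they scale directly with whatever growth is assumed.

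**The case against.** Several points on the other side stand.

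- **The model may not use the visits.** A reader might infer that the planned mixed model already uses every visit, so imputation is merely redundant. The text does not support that: the only repeated factor named is the two eyes, and the summary measure is change at 24 months. If the model holds only that change, a child without a 24-month value contributes nothing, and validity under missing at random through earlier visits does not follow. Deleting the rule is therefore not enough.
- **The fraction imputed is not known.** The 20% are called unevaluable and the sample is inflated for them, which may mean they are left out and only sporadic gaps are filled. The 5% and 10% rows of the first table would then apply. Against this, the rule covers any missing data and the FAS does not exclude dropouts.
- **The variant is not known.** A reader might infer that the primary p-value will certainly be wrong. That goes too far. The size depends on the method, and carry-forward under equal loss attenuates but does not produce excess false positives. Masking and identical packaging give no specific reason to expect a 10% v 30% imbalance.
- **The PPS has some value.** It probably approximates a complete-case analysis, so disagreement with the FAS would be informative. It also selects on adherence, and a child who wore posted lenses but missed a measurement could remain in it with an imputed value.
- **Pandemic losses are not reported.** A reader might infer that axial lengths have already been missed. The text says only that lenses are sent even if visits do not take place, and the 3-, 9-, 15- and 21-month visits include no axial-length measurement.

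**Conclusion.** The concern holds as a fault in a stated rule. The protocol prescribes single imputation, names no variant, exempts no outcome and makes no allowance for imputation uncertainty.

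If 24-month axial lengths are filled, group-mean imputation gives a type I error of about 6%, 8% and 12% at 5%, 10% and 20% missing. This result is algebraic and scale-free. Regression, single-draw or donor imputation gives roughly 8–11% at 20%. Carry-forward leaves the SE no smaller but attenuates a true effect by about 13% under equal 20% loss, and it produces a false difference only when loss differs between arms.

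The figures other than the closed form rest on refraction inputs standing in for axial length, loss completely at random, steady growth and one value per child. Which figure applies depends on the variant chosen and on how many 24-month values are in fact imputed. The protocol fixes neither.

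**What to change.** 1. Delete the single-imputation rule for the efficacy outcomes.
2. State that the primary mixed model uses all observed axial-length changes at 0.5, 1, 1.5 and 2 years in both eyes, with visit and treatment-by-visit terms and eyes nested within child. The 24-month treatment contrast is primary and no values are imputed.
3. Add multiple imputation with a delta or control-based shift as a sensitivity analysis for departures from missing at random, alongside the PPS.

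The change should be made before treatment codes are released to the analysts. It needs no change to recruitment, visits or treatment. The cost is rewording, modest programming, a fuller primary model than the one now described, and somewhat wider confidence intervals: at 20% missing, at most about 1/0.80 = 1.25 times the width that group-mean imputation would report, and less where earlier visits inform the 24-month contrast.
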